## Methods

### Study Design and Setting

This is a multi-site, quasi-experimental study, using a cluster-design sampling strategy. This study adopts a mixed methods approach to assess the efficacy of using the WHO PEN in comparison with a control group that received no intervention and a digital intervention platform. The study is being conducted in urban poor settings in India across 4 sites with differing geographic and sociocultural characteristics. Allocation to study arms will occur at the community (cluster) level. Within each site, community clusters (wards/slum clusters) will be assigned to one of the 3 intervention arms to reduce contamination between participants and to align with local service delivery structures. All eligible individuals within a cluster are enrolled into the arm designated for that cluster.

The study will span 3 years and execute 3 distinct phases to achieve the 3 stated objectives. The interventions will be deployed in the third phase of the study and will include follow-up evaluations at 3 months, 6 months, 9 months, and 12 months post intervention.

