#### Quantitative Data Collection Tools

##### Sociodemographic Characteristics

Information was recorded on age, gender, marital status, educational qualification, occupation, and monthly household income (INR).

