##### Familiarity With the Use of Technology

Data will be gathered on the usage of mobile phones and the ability of the participants to read and send text messages, along with access to the internet.

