### Data Analysis Plan

Interviews and focus groups will be audio-recorded, transcribed verbatim, and translated to English where necessary. A thematic analysis approach will be applied using NVivo software (Lumivero). Triangulation across all the data sources will enhance validity. Data will be analyzed using SPSS (version 29; IBM Corp) and R software (R Foundation for Statistical Computing). Heuristic evaluation will involve the estimation of severity ratings, frequency of usability issues, time taken to complete tasks, and interrater reliability. Descriptive statistics will include means (SDs), medians (IQRs), and proportions to summarize baseline characteristics. Between interventions and control arms, the analysis would be performed by ANCOVA or generalized linear models, adjusting for baseline values, cluster effects, and site-level covariates. Statistical significance will be set at *P*<.05, with 95% CIs.

A generalized linear mixed-effects model will be used to conduct the primary analysis, because the data are clustered and longitudinal in nature. The generalized linear mixed-effects model will include random intercepts for the clusters of communities and the individual study participants to account for the intracluster correlation and repeated measurements over time. Intervention arm, time, and their interaction will be modelled as fixed effects, with study site included as a fixed effect to control for contextual differences. To control the baseline imbalance in outcome variable values, the baseline value will be used as a covariate in the analysis. The maximum likelihood estimation within the mixed-effects framework will handle the missing data in the study, with sensitivity analyses using multiple imputation. Pairwise comparisons among the 3 study arms will be conducted. This will be adjusted for multiple testing using the Holm-Bonferroni method, with statistical significance assessed at 2-tailed α level of .05.

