### Strengths and Potential Limitations

A mixed methods approach will be utilized, integrating insights from behavioral, clinical, and qualitative measures to capture multidimensional outcomes. The human-centered design will ensure the digital intervention is tailored to the context of the target population, enhancing relevance and user engagement. The inclusion of geographically and culturally diverse sites such as Delhi (plains), Dehradun (valley), Chennai (coastal), and Sikkim (hilly) would provide an additional contextual understanding that would support external validity. Moreover, the incorporation of digital monitoring systems facilitates real-time data acquisition and guarantees the integrity of the interventions.

However, this study anticipates certain limitations. The nonrandomized allocation of participants may introduce selection bias, although cluster-based assignment and analytical adjustments will be employed to minimize its effects. Additionally, variations in digital literacy among participants may influence engagement with the intervention. Despite these constraints, the study is expected to yield robust insights into the differential effectiveness, user experience, and implementation feasibility of digital solutions for NCD prevention within the low- and middle-income country-setting contexts.

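### Allocation is not randomised, yet the stated primary model adjusts only for site and baseline outcome, so between-arm estimates remain open to residual confounding by participant characteristics

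*Protocol article*

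**What the plan says.** **Allocation.** Under Study Design and Setting: "Allocation to study arms will occur at the community (cluster) level". Wards or slum clusters within each site go to one of three arms, and every eligible person in a cluster joins that cluster's arm. Strengths and Potential Limitations states the consequence and the safeguard: "The nonrandomized allocation of participants may introduce selection bias, although cluster-based assignment and analytical adjustments will be employed to minimize its effects".

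**Primary model.** Under Data Analysis Plan: "A generalized linear mixed-effects model will be used to conduct the primary analysis". Its random part has intercepts for cluster and participant. Its fixed part is given as "Intervention arm, time, and their interaction will be modelled as fixed effects, with study site included as a fixed effect". To deal with baseline imbalance in the outcome, "the baseline value will be used as a covariate in the analysis".

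**Other between-arm analysis.** A separate sentence in the same section offers ANCOVA or generalized linear models, adjusted for baseline values, cluster effects and covariates at site level. It names no participant-level covariate either.

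**Data on participants.** Sociodemographic Characteristics lists age, gender, marital status, education, occupation and household income. Table 1 places the Sociodemographic and Health Questionnaire at T0 of phase 3. Familiarity With the Use of Technology adds: "Data will be gathered on the usage of mobile phones and the ability of the participants to read and send text messages". That item has no row in Table 1.

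**The concern.** When wards are assigned rather than randomised, each arm takes on the make-up of its wards. If education or income differs between arms and also predicts later self-care beyond what the baseline score shows, part of the estimated arm effect reflects who lives in the wards.

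The protocol itself treats such variables as relevant. A secondary objective looks for sociodemographic factors that influence adoption of the platform, and the limitations section says that digital literacy may affect engagement. It then relies on adjustment in the analysis to limit selection bias, but the model it writes out contains no term for participant mix other than the baseline outcome. At stake are all three pairwise contrasts. A larger sample does not remove a bias of this kind.

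**Working it through.** **1. What each stated term can and cannot do.**

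| Term in the primary model | Removes | Leaves |
|---|---|---|
| Site fixed effect | Differences between the four cities | Differences between wards within a city, which is where allocation takes place |
| Cluster random intercept | Nothing systematic; it models correlation | Between-arm differences in who was enrolled |
| Participant random intercept | Nothing systematic; it models repeated measures | The same |
| Baseline outcome | The part of a confounder already expressed in the baseline score | Its further effect on later change |

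No matching, weighting or propensity score is described in the article.

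**2. The plan's own figures** (sample size paragraph under Objective 3).
- Design effect: 1 + (30 − 1) × 0.02 = 1.58, as stated.
- Total: 64 × 30 = 1,920, and 1,920 / 0.80 = 2,400, as stated (20% attrition).
- Power inputs alone: d = 0.30 with 80% power at two-sided 5% needs 175 per arm. 175 × 1.58 = 276.5, rounded up to 277, and three arms give 831. After attrition this is 978 (15%) to 1,039 (20%).

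The planned size is well above that requirement, so sampling error is not the weak point.

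**3. Standard error for one contrast.** I take 1,920 analysed and an even split, 1,920 / 3 = 640 per arm. The even split is an approximation, since 64 clusters do not divide by 3.

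SE = √(2 × 1.58 / 640) = 0.0703 SD

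This ignores any gain in precision from baseline adjustment and repeated measures.

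**4. Illustrative residual bias.** None of these inputs is in the documents:
- g: effect of the covariate on the follow-up outcome given baseline, in outcome SD per covariate SD; 0.1 to 0.3 assumed.
- D: between-arm imbalance in the covariate, in SD; 0.2 to 0.5 assumed.
- r: correlation of the covariate with the baseline outcome; 0 to 0.5 assumed.

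If the arms differ in baseline outcome only through this covariate, that difference is rD. Adjusting for baseline outcome then removes r × rD of the covariate imbalance:

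bias = g × (D − r²D) = g × D × (1 − r²)

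| g | D | r = 0 | r = 0.5 | Share of d = 0.30 |
|---|---|---|---|---|
| 0.1 | 0.2 | 0.020 | 0.015 | 7% to 5% |
| 0.2 | 0.3 | 0.060 | 0.045 | 20% to 15% |
| 0.3 | 0.3 | 0.090 | 0.068 | 30% to 23% |
| 0.3 | 0.5 | 0.150 | 0.113 | 50% to 38% |

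The range is 0.015 to 0.15 SD.

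**5. Effect on false positives, again only as illustration.** A bias of 0.06 SD is 0.06 / 0.0703 = 0.854 SE, and 0.09 SD is 1.281 SE. For a single contrast tested at two-sided 5%, rejection with no true effect would be about 14% and 25%. The plan uses Holm-Bonferroni. At its first step (0.05/3, critical value 2.394) the same shifts give about 6% and 13%, against 1.7% without bias.

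**The case against.** **The article is condensed.** It says what the model will include, not that nothing else may enter, and a full covariate list is often left to an analysis plan that is not shown. This weakens the point but does not remove it. The article writes its model out term by term and ties the baseline covariate to imbalance in the outcome. It also relies on adjustment against selection bias, and the adjustment it specifies does not address participant mix.

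**Some protection exists.** All three arms run in every site, site is a fixed effect, 64 clusters are spread over the arms, and baseline outcome is adjusted for. All participants must have a mobile phone and be willing to use technology, which narrows one likely imbalance. This stands, and it is why the claim is limited to residual confounding.

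**Stronger readings that the documents do not support.**
- A reader might infer that the arm effects are confounded, or that these variables will differ between arms. The documents do not describe how wards are chosen and give no data by arm.
- A reader might infer that the 5% error becomes 14% to 25%. Those figures rest on assumed inputs and on one unadjusted contrast; under Holm's first step they are about 6% and 13%.
- A reader might infer that every desirable covariate is already collected at baseline. Technology familiarity is not in Table 1. Disease group is implied by the eligibility criteria but is not listed as a recorded variable.
- A reader might expect adjustment to tighten the intervals. Covariates correlated with arm can widen them.
- A reader might call the site-level covariates redundant. The site fixed effect is stated for the mixed model, whereas that phrase belongs to the ANCOVA/GLM sentence, which states no site fixed effect.

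**Conclusion.** The point holds in limited form. The study is not randomised by its own account, and it relies on analysis to limit selection bias. The stated primary model adjusts only for site and the baseline outcome value, although participant variables are scheduled at T0. The between-arm estimates therefore remain open to residual confounding by participant characteristics.

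The documents do not allow its size to be computed. The range of about 0.015 to 0.15 SD, or 5% to 50% of d = 0.30, rests on assumed slopes, imbalances and correlations. It also assumes that the arms differ in baseline outcome only through the omitted covariate. This should be corrected before phase 3 outcomes are seen, because covariates chosen afterwards invite selective adjustment.

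**What to change.** 1. Prespecify age, gender, education and household income, as recorded at T0, as fixed covariates in the primary mixed model.
2. Add disease group and technology familiarity once their collection at phase 3 baseline is confirmed. If technology familiarity is to be measured then, give it a row in Table 1.
3. Add a sensitivity analysis with propensity-score weighting on the same list, and report baseline characteristics by arm.
4. Keep the site-level covariates in the ANCOVA/GLM sentence unless a site fixed effect is also stated there; otherwise that analysis could lose its only site adjustment.

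**Cost.** The sample size stays at 2,400. The model gains a few parameters, about ten if all six variables are used, against 1,920 analysed participants. Intervals may widen slightly where covariates are correlated with arm. Under a non-linear link the arm effect becomes conditional on the added covariates, which the report should say. Items 1, 3 and 4 need only a change of wording in the analysis section; item 2 may also need a change to the baseline data collection.

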The sample size was determined to detect differences in primary outcomes (health-seeking behavior and NCD self-management) between the 3 arms. The initial sample size was adjusted for the cluster design, considering Cohen *d* as 0.30 for a small to moderate effect size, with 80% power and a significance level of 5%. Each study site will include 16 community clusters, resulting in a total of 64 clusters across the 4 sites. From each cluster, nearly 30 participants will be included with intracluster correlation coefficient of 0.02 and design effect of 1.58. The sample size will be adjusted for 15%-20% of attrition rate during the 12 months of follow-up period, resulting in the total sample size of 2400 (600 per site).

The comparative evaluation across these 3 groups will reveal differential effects on health-seeking behavior, self-management practices, and clinical outcomes. Figure 1 illustrates the study design framework, detailing the phases of data collection and intervention implementation. The summary of the quantitative data collection tools and outcome measures in the third phase of the study are described in Table 1.

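### Holm-Bonferroni is valid for the three pairwise arm comparisons, but Shaffer's modification is never less powerful at the same 5% familywise error

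*Protocol article*

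**What the plan says.** The Protocol article, Methods, Data Analysis Plan, names the family, the procedure and the error rate. The family: "Pairwise comparisons among the 3 study arms will be conducted". The procedure: "This will be adjusted for multiple testing using the Holm-Bonferroni method". The level: "with statistical significance assessed at 2-tailed α level of .05".

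The sample-size paragraph under Data Collection and Sampling Strategy (Objective 3) gives the figures needed to judge what this choice costs. The effect is stated as "considering Cohen *d* as 0.30 for a small to moderate effect size", with 80% power at a 5% level. The plan has 16 clusters at each of the 4 sites, 64 in all. On cluster size and clustering it says that "nearly 30 participants will be included with intracluster correlation coefficient of 0.02 and design effect of 1.58". Attrition and total are given as "15%-20% of attrition rate during the 12 months of follow-up period, resulting in the total sample size of 2400 (600 per site").

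The paragraph does not say which pair of arms the 0.30 refers to, and it gives no expected pattern for the three arm means.

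**The concern.** For three ordered P values Holm uses .05/3, .05/2 and .05. These thresholds allow for any subset of the three null hypotheses being true together. With three arms that cannot happen. If control, WHO PEN and digital are not all equal, at most one pair can be equal, because two equal pairs would force the third. After one rejection, at most one true null can remain, so no further division of alpha is needed. Holm's .025 at the second step guards against a configuration that does not exist.

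What is at stake is power for the second-ranked comparison. The Rationale and Discussion present digital versus WHO PEN as a main question of the study. If WHO PEN has some benefit over control, the digital versus WHO PEN difference is smaller than digital versus control and will often rank second.

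**Working it through.** **Step 1. Reproduce the plan's own figures.** Design effect: 1 + (30 − 1) × 0.02 = 1.58, as stated. Clusters × size: 64 × 30 = 1920. Attrition at 20%: 1920 / 0.80 = 2400, as stated.

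**Step 2. Effective size per arm.** The article does not say how clusters divide between arms, so equal arms are assumed. With 1920 analysed: 1920 / 3 / 1.58 = 405. The standard error of a pairwise difference, in SD units, is √(2/405) = 0.070.

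**Step 3. Unadjusted power at the stated effect.** Power ≈ Φ(0.30/0.0703 − z). This gives 99.0% at .05, 97.9% at .025 and 97.0% at .05/3. The trial is large for d = 0.30. For 80% power at .05, that effect needs 175 per arm; 175 × 1.58 = 277; with 15% to 20% attrition, 326 to 347 per arm, or 978 to 1041 in total. This is why the difference between the procedures is small at d = 0.30.

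**Step 4. The two procedures.**
- Holm: P(1) ≤ .05/3, then P(2) ≤ .05/2, then P(3) ≤ .05.
- Shaffer: P(1) ≤ .05/3, then P(2) ≤ .05 and P(3) ≤ .05.

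The first step is identical and no later Shaffer threshold is below Holm's. Shaffer therefore rejects everything Holm rejects, and the chance of at least one rejection is the same.

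**Step 5. Simulation.** Three normal arm means, equal arms, 405 effective per arm, one outcome at one visit, known variance, at least 400,000 replicates per scenario. Means are control/WHO PEN/digital.

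| True means | Contrast | Holm | Shaffer | Gain (points) |
|---|---|---|---|---|
| 0/0/.30 | digital vs control, digital vs PEN | 97.8% | 98.6% | 0.8 |
| 0/.30/.60 | each pair | same | same | 0.0 |
| 0/.10/.30 | digital vs PEN (.20) | 75.1% | 80.7% | 5.6 |
| 0/.15/.30 | each .15 contrast | 50.8% | 56.7% | 5.9 |
| 0/.20/.20 | each active arm vs control | 70.7% | 75.1% | 4.4 |

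In no replicate did Holm reject a pair that Shaffer did not.

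**Step 6. Error control.** Under the global null the familywise error is 4.4% for both procedures. With means 0/0/.30, the one true null is rejected in 4.7% (Holm) and 5.0% (Shaffer).

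**Step 7. Sensitivity to the number analysed.** With 1536 analysed (24 per cluster, design effect 1 + 23 × 0.02 = 1.46), the gain for 0/0/.30 is 1.4 points. With 2400 analysed (37.5 per cluster, design effect 1.73), it is 0.4 point. For 0/.15/.30 the gain on each .15 contrast is 6.8 and 4.7 points. Over all scenarios run, the gain per contrast lies between 0.0 and 7.4 points.

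**The case against.** The strongest reply is that nothing here is wrong. Holm is a recognised procedure with strong control of the familywise error, it contradicts nothing else in the article, and at the only effect size the article states the gain is under one point. All of that stands. What remains is that the article itself fixes both the family and the procedure, and for that family a procedure exists that is never worse and sometimes better. There is no trade-off to weigh.

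A second objection is that the power figures come from one outcome at one visit with equal arms. The planned primary analysis is a longitudinal mixed model with baseline adjustment. This also stands: the percentages are illustrative. The dominance of Shaffer over Holm does not depend on them, because it follows from the thresholds and the logical link alone.

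Two stronger arguments might be inferred, and neither holds.
- A 2-df test of equality of the three arms at .05, followed by each pair at .05, is not equivalent to Shaffer and does not dominate Holm. Suppose arms are equal in size, the middle mean lies exactly midway and the extreme pair has z = 2.42. The pair's P is .0155, below .0167, so Holm rejects. The global statistic is 2.42² = 5.86, below 5.99 (P = .053), so the closed test stops without a rejection.
- Comparing a flat .025 test with a flat .05 test suggests a cost of about 21% more participants: (2.241 + 0.842)² / (1.960 + 0.842)² = 1.21. That overstates the cost, since Holm tests the last-ranked pair at .05 and Shaffer must still pass the first step at .05/3.

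**Conclusion.** The point holds as an optional efficiency improvement. Holm's second threshold is stricter than three linked hypotheses require, and Shaffer's modification removes the excess at the same 5% familywise error within each family of three pairs.

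A reader might infer a fixed loss of 4 to 6 points of power. The article does not support that. At 405 effective per arm, the gain is about 0.8 point when one arm differs by 0.30 from two equal arms (0.4 to 1.4 over 2400 to 1536 analysed). It is nil for means 0/.30/.60 and nil for the chance of at least one rejection. Gains of about 4 to 6 points arise for contrasts of .15 to .20, for example digital versus WHO PEN when WHO PEN lies between control and digital. Such contrasts are plausible with an active comparator, but they are assumptions and not figures in the article.

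The sizes rest on equal arms, a normal approximation and a single outcome and visit.

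**What to change.** In the Data Analysis Plan, replace the sentence naming Holm-Bonferroni with:

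*The three pairwise comparisons will be adjusted by Shaffer's modification of Holm (smallest P against .05/3; if rejected, the other two each against .05), at 2-tailed familywise α of .05.*

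Apply it to the same family of three pairs to which the plan now applies Holm. The change does not settle how alpha is handled across outcomes or visits, and it leaves that matter as it is. Any statement of benefit should say that the gain depends on the arm pattern.

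The cost is one sentence and a few lines of R, with no added participants and no loss of error control. The Results section reports only phase 1 data collection, so the change can be made before phase 3 outcome data exist.

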### Project Timelines

The project duration will be 3 years, from January 2025 to January 2028. A comprehensive overview of the timelines of the different phases of the project is provided in Table 2.

**Table 2 table2:** Scheduled timeline of the tasks in the study.

Tasks		Months											
		1	2-3		4-6		7-14	15-20^a^			32-33	34-36	
Phase I													
	Literature review, designing, and planning of the study, and stakeholder meeting	✓											
	Qualitative data (in-depth interviews/focus group discussions) and quantitative data collection (Knowledge, Attitude, and Practice)	✓	✓	✓									
	Analysis of mixed data		✓	✓									
Phase II													
	Development intervention					✓							
	Heuristic evaluation					✓							
	Usability of the developed digital intervention system					✓							
	Refinement					✓							
Phase III													
	Final deployment of the proposed digital and WHO PEN^b^ intervention								✓				
	Study recruitment								✓				
	Baseline and follow-up data collection								✓				
	Data preparation and statistical analysis									✓			
	Report writing and manuscript preparation									✓			✓
	Dissemination of research findings												✓

^a^Follow-up until week 32.

^b^WHO PEN: World Health Organization Package of Essential Noncommunicable Diseases.

